### Study Design

The evaluation will use a mixed methods approach, guided by the RE-AIM (Reach, Effectiveness, Adoption, Implementation, and Maintenance) framework [31]. Effectiveness will be assessed using a pragmatic single-arm, pre-post study design.

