##### Chronic Disease Risk Factors

The impact of Wellness my Way on consumers’ chronic disease–related risk factors and diagnosis was assessed at program intake via the health and well-being assessment and 6 months post engagement with Wellness my Way via a digital or phone survey. Data were collected by Queensland Health’s HCC’s Microsoft Dynamics 365 CRM. Both the health and well-being assessment and the 6-month survey measured diabetes risk using a modified version of the Australian Diabetes Risk Assessment Tool (AUDRISK) [24], mental health using an ultra-brief screening tool (4-item Patient Health Questionnaire [PHQ-4]) [25], physical activity engagement using The Active Australia Survey [26], and other modifiable risk factors such as drug and alcohol use and biometrics.

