#### Consumers

Consumers’ satisfaction and experience with the Wellness my Way pilot were collected via the Patient Reported Experience Measures survey following the health and well-being assessment or telephone coaching call. The survey was sent to consumers who completed the model of care and those who drop out after the health and well-being assessment. Consumers were asked to provide feedback on the prevention model of care via level of agreement using Likert scale items and open text responses.

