### Statistical Analysis

All quantitative reach, effectiveness, adoption, and implementation outcomes will be described using descriptive statistics. *χ*^2^ tests of association will be used to examine associations between categorical variables, and paired independent *t* tests and McNemar tests will be used to examine changes in continuous and categorical outcomes, respectively, between program intake and at 6 months. To be eligible to be included in the quantitative evaluation, participants must have been eligible for their 6-month follow-up at the close of the pilot implementation phase. Intention-to-treat analysis will be followed to handle missing data. The effectiveness outcome will be treated as exploratory given the pilot study design and absence of randomization or a comparison group.

All qualitative implementation data will be analyzed according to Braun and Clarke’s [32] approach to thematic analysis. Audio-recorded qualitative data will be transcribed verbatim, checked for accuracy, and deidentified for anonymity. Using NVivo 14 (version 14.3.2; Lumivero), researchers will generate initial codes and meet to group codes into relevant themes. Themes will be refined, and subthemes may be generated to assist interpretation of findings. Open-ended responses will be analyzed using content analysis [33].

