### Strengths and Limitations

A strength of the development, implementation, and evaluation protocol for the Wellness my Way pilot is the multisectoral partners across health, government, and academia to design and codeliver the prevention model of care. The evaluation is guided by components of the RE-AIM implementation framework [31], with data collection embedded within program delivery. Reliance on self-report data collected via the health and well-being assessment (eg, chronic disease risk factors) and program engagement data (varied data availability) may introduce response bias. The pragmatic nature of evaluating routine service delivery also means that a single-arm, pre-post study design was used, with more rigorous methods such as those with comparison groups or randomization not feasible.

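### Intention-to-treat is named as the way to handle missing 6-month data, but it supplies no missing value, and the paired tests as written would cover only consumers with both assessments

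*Protocol article*

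**What the plan says.** The Study Design section fixes the design: "Effectiveness will be assessed using a pragmatic single-arm, pre-post study design". Risk factors are measured at intake and again "6 months post engagement with Wellness my Way via a digital or phone survey" (Chronic Disease Risk Factors), so a consumer who does not answer that survey has no 6-month value.

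The Statistical Analysis section then makes four statements in one paragraph:

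- On the tests (the closing figure counts months): "paired independent *t* tests and McNemar tests will be used to examine changes in continuous and categorical outcomes, respectively, between program intake and at 6".
- On who is included: "participants must have been eligible for their 6-month follow-up at the close of the pilot implementation phase". The condition is being due for follow-up, not having completed it.
- On missing data: "Intention-to-treat analysis will be followed to handle missing data". The article has no other missing-data provision.
- On status: "The effectiveness outcome will be treated as exploratory given the pilot study design and absence of randomization or a comparison group".

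Attrition is foreseen. The experience survey is also sent to "those who drop out after the health and well-being assessment" (Consumers), although no rate is given. The Strengths and Limitations section says that self-report and "program engagement data (varied data availability) may introduce response bias", but it does not mention loss to the 6-month survey.

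**The concern.** Intention-to-treat answers the question of who is analysed and, in a comparative trial, in which group. It does not say what stands in for an outcome that was never observed. That is so in any design. With one arm and no randomisation there is not even an allocation to preserve, so the phrase can only mean that everyone who meets the inclusion rule is kept.

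The tests named beside it cannot do that unaided, because each needs a value at both times. The paragraph therefore defines one set of people and names tests that, without a fill-in rule, use a smaller one.

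What is at stake is the reading of research objective 3, the impact on chronic disease risk factors. A change estimated in responders but labelled intention-to-treat would be taken to apply to everyone included. The article says that the findings will inform possible scale-up.

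**Working it through.** The article states no sample size, effect size, standard deviation or response rate, so there is no figure of the plan's own to reproduce. The point rests on the text; the numbers after step 4 only illustrate it.

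**Reading the paragraph**

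1. The included set is everyone due the 6-month follow-up by the stated cut-off, whether or not they responded.
2. The tests are the paired t test and the McNemar test. The article's wording joins paired and independent; it is read here as paired, since change within the same people is the aim. Each test uses only complete pairs.
3. The 6-month value comes only from the survey, so non-response removes a person from both tests.
4. To keep the set in step 1, some rule must fill in or model the missing values. Intention-to-treat is not such a rule, and no other is named.

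**Illustration (all inputs assumed)**

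Let f be the share responding, dR the mean change in responders and dN the mean change in non-responders, in units of the SD of change. Take dR = 0.30.

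- Complete pairs estimate dR = 0.30 at every f.
- The mean over everyone included is f × dR + (1 − f) × dN.

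| f | Complete pairs | All included, dN = 0.30 | All included, dN = 0 | All included, dN = −0.20 |
|---|---|---|---|---|
| 0.3 | 0.30 | 0.30 | 0.3 × 0.30 = 0.09 | 0.09 − 0.7 × 0.20 = −0.05 |
| 0.5 | 0.30 | 0.30 | 0.5 × 0.30 = 0.15 | 0.15 − 0.5 × 0.20 = 0.05 |
| 0.7 | 0.30 | 0.30 | 0.7 × 0.30 = 0.21 | 0.21 − 0.3 × 0.20 = 0.15 |

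With dN = 0 the ratio of the reported to the all-included change is 1/f: 0.30/0.09 = 3.3 at 30% response and 0.30/0.21 = 1.4 at 70%. With dN = 0.30 it is 1.

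**Binary outcome (assumed)**

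Suppose 200 are included, 20% of responders improve and 10% worsen. At 30% response there are 60 pairs, 12 improved and 6 worsened. The net change is 6/60 = 10 points in responders, but 6/200 = 3 points over all included if non-responders are unchanged. At 70% response there are 140 pairs, 28 improved and 14 worsened, giving 10 points against 14/200 = 7 points. The McNemar statistic is the same under both readings, (12 − 6)²/18 = 2.00 and (28 − 14)²/42 = 4.67, because unchanged people add no discordant pairs. The p-value therefore cannot show which estimate is being reported.

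**The case against.** **The text never says that only responders will be analysed.** This is true. It is an inference from how the tests work. Inclusion is by being due for follow-up, and the authors may intend an unstated imputation before the paired tests. A reader might infer a planned responder-only analysis; the article does not support that. What it supports is that the stated rule does not determine the analysis, and that the tests taken as written do not cover the stated set.

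**A journal article may leave the method to an unseen analysis plan.** That would excuse silence. Here a method is named, and what is named is not a missing-data method.

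**The overstatement is assumed.** This stands. A reader might take 1.4 to 3.3 times as the expected bias. It is simply 1/f under an assumed response rate and an assumed zero change in non-responders. With equal change there is no bias, and the documents do not say which case applies.

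**Carrying intake values forward.** A reader might suppose that the intake value would be carried forward and that the test would then look too significant. The article names no such rule, and the second step does not follow. With dR = 0.30, the carried-forward SE is f × √(1.09 − 0.09f) times the complete-pairs SE, that is 0.31 at f = 0.3 and 0.71 at f = 0.7. But the estimate is also multiplied by f, so the t statistic is 1/√(1.09 − 0.09f) of its complete-pairs value, or 0.97 to 0.99. The smaller SE is therefore not evidence of inflated significance, and McNemar's statistic does not change at all.

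**Effectiveness is exploratory and the primary outcome is a count.** Both are true, and they lower the priority. They do not make the label accurate.

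**Conclusion.** The point holds as a defect in what the article states. The rule offered for missing data defines an analysis set at most, and the tests beside it would, as written, leave out part of that set while the result kept an intention-to-treat label.

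The size of any bias cannot be derived from the documents. It depends on the 6-month response rate and on how non-responders changed, neither of which is given. Under the assumptions shown it runs from none to a reported 0.30 SD where the mean over all included is 0.09 to 0.21 SD. If non-responders worsened by 0.20 SD, that mean would be −0.05 to 0.15 SD.

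This should be fixed before the analysis is run, but it is not critical. It touches only the exploratory 6-month risk-factor outcomes under objective 3. The primary reach outcome is unaffected.

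**What to change.** Replace the intention-to-treat sentence with the following elements:

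1. **Analysis set.** All consumers due the 6-month follow-up under the inclusion rule already in the Statistical Analysis section, whether or not they responded.
2. **Main estimate.** Change from intake to 6 months by a likelihood-based mixed model (linear for continuous, logistic for binary outcomes) or by multiple imputation, with missing at random stated as the assumption. Use the demographics and baseline risk factors collected at intake to support it. Ordinary unweighted GEE is not a substitute, because it generally needs a stronger assumption about missingness.
3. **Supportive tests.** Keep the paired t and McNemar tests, labelled as responders only.
4. **Reporting.** Give the 6-month response rate and compare responders with non-responders on intake characteristics.
5. **Sensitivity analysis.** One analysis in which non-responders have no mean change. It is needed because the main estimate removes bias only under missing at random. In the illustration with dN = 0 it would still be about 0.30 SD unless intake data explain the difference.

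The cost is a little more analysis work. No new data are required, since the intake variables are already collected as part of the programme.

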### Ethical Considerations

Wellness my Way is a Queensland Government–funded health service program delivered collaboratively by HWQld and Queensland Health. All aspects of program delivery are routine service delivery, and all data collected from consumers were routinely collected data as part of that routine service delivery. At program enrollment, all consumers provided consent for their data to be collected and used for program delivery, evaluation, and future research purposes. Consumer data were routinely collected and securely stored within Queensland Health systems from July 2024 as part of standard program operations. Ethical approval to access these routinely collected data for research purposes was provided by the Metro North Health Human Research Ethics Committee (HREC/2025/MNH/121442; SSA/2025/QHC/121442) on December 24, 2025. Deidentified consumer data will be transferred to HWQld and UQ upon completion of the pilot.

Ethics approval for all qualitative research activities with stakeholders, including workshops, focus groups, and interviews, was obtained from UQ Human Research Ethics Committee (2025/HE000769) on June 13, 2025. All participants in stakeholder consultation were asked to provide prospective informed consent for data collected during consultation to be used for research purposes. Stakeholders who did not provide informed consent were still able to participate in consultation, without their data being used for research purposes.

Data sharing between HWQld, Queensland Health, and UQ was undertaken in accordance with approved ethics, governance, and data sharing agreements. Quantitative consumer data are stored in Queensland Health systems, and only authorized, ethics-approved researchers have access to deidentified data for research purposes upon completion of the pilot. Qualitative data are stored within UQ’s Research Data Manager and only accessible to authorized, ethics-approved researchers for analysis and reporting, in accordance with institutional and national research ethics requirements.

## Results

The Wellness my Way pilot evaluation concluded on January 29, 2026, with results expected to be shared in the second half of 2026. Findings from both quantitative and qualitative analyses will be disseminated in internal reports, conference abstracts, and scientific publications (with authorship determined according to scientific authorship guidelines). Findings will be shared with the pilot’s Connectors as well as consumers via websites, social media, online newsletters, and written reports.

## Discussion

### Principal Findings

This program evaluation will provide key insights to determine whether Wellness my Way has connected people at risk of or living with noncommunicable diseases with free and low-cost prevention programs across South West Queensland. It is expected that Wellness my Way will improve uptake of local and state prevention programs among the pilot population. Findings will inform ongoing program delivery and provide insights into program scalability.

### Comparison to Prior Work and Contribution to the Evidence Base

The Wellness my Way pilot evaluation will occur in collaboration between government entities and university partners, enabling evidence-informed strategic planning across multisectoral partners to strengthen systems and services with the capacity to deliver Wellness my Way at scale. This collaboration is key to generating practice-based evidence, improving the understanding of the impact of community-led prevention programs, and addressing the knowledge-to-practice gap.

National and state governments have called for multisector collaboration to meet the high demands of the health care system [12], particularly in response to the growing burden of chronic disease. Similar work [34] has illustrated how multisector partnerships can codeliver and evaluate a community-delivered health promotion intervention; however, they are often not reported in the scientific literature nor supported by robust evaluation. The current approach ensures that these important and novel approaches to community health promotion are well-documented, described, and evaluated, so that learnings can be disseminated and inform other initiatives, as well as scale up.

### Strengths and Limitations

A strength of the development, implementation, and evaluation protocol for the Wellness my Way pilot is the multisectoral partners across health, government, and academia to design and codeliver the prevention model of care. The evaluation is guided by components of the RE-AIM implementation framework [31], with data collection embedded within program delivery. Reliance on self-report data collected via the health and well-being assessment (eg, chronic disease risk factors) and program engagement data (varied data availability) may introduce response bias. The pragmatic nature of evaluating routine service delivery also means that a single-arm, pre-post study design was used, with more rigorous methods such as those with comparison groups or randomization not feasible.

### Future Directions and Dissemination

Findings from the Wellness my Way pilot evaluation in South West Queensland will inform the potential for scale-up. Dissemination will include peer-reviewed publications, conference presentations, government reports, and plain language summaries for community partners.

### Conclusions

The development, implementation, and evaluation of a pilot prevention model of care within South West Queensland with high unmet needs of chronic disease offers the opportunity to enhance the knowledge of community-based prevention and understand the influence on the uptake of prevention programs. The evaluation will inform the feasibility of Wellness my Way, with findings anticipated to inform potential scale-up via multisector collaborations.
